## Abstract

**Background:**

Sepsis is still a common critical disease with high morbidity and mortality in intensive care unit. Despite published guidelines for sepsis, development of antibiotic therapy and advanced organ support technologies, the mortality of sepsis patients is still 25% or more. It is necessary to distinguish the subtypes of sepsis, and the targeted therapy for the patients need to be explored. Platelets have various biological functions in hemostasis and thrombosis, host defense, inflammatory/immune responses and tissue repair/regeneration. Moreover, severe thrombocytopenia or sustained thrombocytopenia was closely associated with multiply organ dysfunction and higher mortality in sepsis patients. The clinical therapies for thrombocytopenia are platelet transfusion and platelet-elevating drugs. However, platelet transfusion has many defects in clinical practice in sepsis patients, and the impact of platelet-elevating drugs for sepsis patients is still unclear. RESCUE trial is aim to explore the effect of a platelet-elevating drug, recombinant human thrombopoietin (rhTPO), as an effective rescue therapy on sepsis patients with acute severe thrombocytopenia.

**Methods:**

It is a randomized, open-label, multi-center, controlled trial in 5 tertiary academic hospitals including medical, surgical or general ICUs. In this study, a total of 200 sepsis patients with severe thrombocytopenia will be randomly assigned in a 1:1 ratio to the control and rhTPO group. The patients will be followed up to 28 days after randomization. All patients in two groups receive the same treatment based on the guideline of Surviving Sepsis Campaign. Primary outcome is 28-day mortality. Secondary outcomes are the changes of PCs, blood transfusion, biomarkers of infection and organ function, days free from advanced organ support, drug-related adverse events, the length of ICU and hospital stay.

**Discussion:**

RESCUE trial is the first randomized controlled trial to explore the impact of rhTPO for severe thrombocytopenia in sepsis patients diagnosed by sepsis-3.0 standard. Furthermore, RESCUE trial results will be of significant clinical value on the targeted therapy and add clinical evidence that rhTPO is an effective rescue therapy for these sepsis patients.

**Trial registration:**

ClinicalTrials.gov: NCT02707497. Registered Date: March 3rd, 2016. Protocol Version 3. Protocol Date: January 25th, 2019.

## Background

Sepsis defined as infection-induced organ dysfunction is a common critical disease with high mortality and is the leading cause of death in intensive care unit [1, 2]. Furthermore, the incidence of sepsis in ICU is increasing year by year, reaching more than 30% [3–5]. In recent decades, despite published guidelines for sepsis, rapid development of antibiotic therapy and advanced organ support technologies, the mortality of sepsis patients is still 25% or more [6]. There have been many large RCT clinical studies targeting to improve the prognosis of sepsis [7–10]. Unfortunately, these studies all had negative results and no therapy have been found to improve clinical outcomes in sepsis patients. It could be ascribed to that sepsis is a critical disease caused by many different etiologies which is involved in different pathophysiological changes. Besides, in most past studies, sepsis patients diagnosed by the standards with poor specificity had poor homogeneity. Therefore, to improve clinical outcomes of sepsis patients, distinguishing different subtypes of sepsis and developing targeted therapy for the certain subtypes need to be explored.

Platelet counts (PCs) are frequently altered in patients with sepsis, and are implicated in the pathogenesis of multi-organ failure. Thrombocytopenia is common in sepsis patients, the incidence of which is even as high as 55% [11]. There exist the following mechanisms about sepsis-related thrombocytopenia [12, 13]:1) Some toxins and inflammatory mediators induced by sepsis can inhibit the formation and release of megakaryocytes in bone marrow to cause thrombocytopenia; 2) Some toxins and inflammatory mediators induced by sepsis can directly destroy platelets; 3) Sepsis is often accompanied with local microthrombosis or even cause disseminated intravascular coagulation (DIC) to result in massive platelet depletion; 4) Thrombocytopenia can be induced by some clinical treatments for sepsis patients such as renal replace therapy (RRT), heparin and antibiotics. Until now, it has been confirmed that platelets have various biological functions, not only in hemostasis and thrombosis but also in the host defense, inflammatory/immune responses, tissue repair and regeneration [14–16]. Clinically, thrombocytopenia was closely associated with multiply organ dysfunction and the higher mortality in sepsis patients [17, 18]. Moreover, a multicenter prospective trial in France pointed out that thrombocytopenia was an early prognostic indicator for sepsis patients, and the occurrence and duration of thrombocytopenia were closely related to length of ICU stay, hospitalization stay and 28-day mortality. Furthermore, the greater the extent of thrombocytopenia was, the higher the mortality was [19]. Another study found that severe thrombocytopenia released more inflammatory factors, stimulated endothelial cells, inhibited leukocyte adhesion/activation related signaling pathways, activated complement related signaling pathways, and caused dysregulated host defense responses. Furthermore, 30-day mortality of sepsis patients with severe thrombocytopenia was more than 50% [20]. In our previous meta-analysis study, we also found that thrombocytopenia was associated with poor prognosis and increased the complication including shock, bleeding and acute kidney injury in sepsis patients [21]. Besides, the patients who had sustained thrombocytopenia or a drop-in PCs of > 30% during ICU had the higher mortality [22]. The longer the duration of thrombocytopenia is, the worse the prognosis of these patients have, and rapid recovery of PCs may reduce the mortality of these patients. In our single-center, retrospective cohort study, we found that sepsis patients with severe thrombocytopenia might have the more blood product transfusion, the shorter days free from organ support, the shorter survival days and the higher 28-day mortality. Therefore, there is an urgent need to explore a safe, effective therapy for recovery of PCs in sepsis patients with thrombocytopenia, especially severe thrombocytopenia.

The most common clinical therapy to increase PCs is platelet transfusion. Theoretically, one standard unit dose of platelet transfusion can increase PCs by 20 X10^9^/L. However, because of resource scarcity, transfusion-related immune and infectious complications, ineffective transfusion and platelet antibody production, platelet transfusion is limited in clinical practice and has a rigorous indication in sepsis patients [6, 23]. So, platelet-elevating drugs probably as the rescue therapy improve the prognosis of sepsis patients with thrombocytopenia through recovering PCs.

Thrombopoietin as a highly specific platelet-stimulator can directly act on bone marrow hematopoietic stem cells and bind to its specific receptor Mpl. TPO can stimulate all stages of megakaryocyte formation and specifically increase PCs [24, 25]. In addition, some studies showed that TPO improved T lymphocyte function, regulated the release of inflammatory mediators, reduced endothelial cell injury, decreased platelet aggregation and consumption [26]. Recombinant human thrombopoietin (rhTPO) is a full-length glycosylated-TPO produced by Chinese hamster ovary cells, which has the similar biological functions as endogenous TPO. It has been confirmed that rhTPO could effectively increase PCs in patients with immune or chemotherapy-related thrombocytopenia and has no serious adverse effects [27–29]. Recently, Kong Z et al. reported that rhTPO effectively increased PCs in pregnancy patients with immune thrombocytopenia and had no adverse effects, which suggests that rhTPO is a safe drug [30]. However, to date, there are very few studies about the impact of rhTPO for sepsis patients, especially prospective RCT study. Meanwhile, the appropriate patients, using course and safety of rhTPO in sepsis are also still unclear. In our previous retrospective study, for patients with severe thrombocytopenia, rhTPO could rapidly increase PCs, reduce 28-day mortality, and there were no severe adverse events during rhTPO treatment. However, there were several limitations in the study, which was a retrospective, single-center study; the sample size was small and the patients were non-randomized. So, the purpose of this study is to confirm the clinical effect of rhTPO on sepsis patients with severe thrombocytopenia.

## Methods and design

### Objectives

The objective of this study is to determine whether rhTPO as an effective and safe rescue therapy rapidly increases the platelets counts, shortens recovery time of platelets, reduces platelets transfusion and bleeding events, and improves the prognosis in sepsis patients with severe thrombocytopenia.

### Study design and setting

The study is designed as a randomized, open-label, multi-center, controlled study in 5 tertiary academic medical centers which are medical, surgical or general ICUs. [name]. W (Shanghai General Hospital, China) will coordinate all the operational processes and [name]. Y (Shanghai Jiao Tong University School of Medicine, China) will conduct all the statistical analyses. Eligible patients who give their consent to participate in the study will be randomly assigned in a 1:1 ratio to treat with rhTPO (rhTPO group) or without any platelet-elevating drugs (control group). Both two groups receive appropriate medical treatment according to the current guideline of Surviving Sepsis Campaign (SSC) [6], and will be assessed for the outcomes at baseline, after the intervention and at 28-day follow-up. The end of the study is defined by the last follow-up of the last enrolled patient.

Patients in rhTPO group will be treated with rhTPO (TPIAO™, Shenyang Sunshine Pharmaceutical Co., Ltd. Shengyang, China) at a dose of 15000u/d, subcutaneous injection, for 7 consecutive days. RhTPO in the study is for free. The time from randomization to administration of rhTPO will be within 24 h. The drug will be terminated when PCs reach the standard of clinical recovery of platelets (PCs ≥100 × 10^9^/L or the increasing of PCs ≥ 50 × 10^9^/L lasting for at least 3 days) or severe adverse effects happened. The clinical recovery time of platelets was defined as the time it takes to reach clinical recovery. Patients in control group will not be treated with any platelet-elevating drugs.

In both control and rhTPO groups, there is the same standard of platelet transfusion: when PCs are below 10 × 10^9^/L in the absence of apparent bleeding; or below 20 × 10^9^/L if the patient has a significant risk of bleeding; or below 50 × 10^9^/L if the patient has active bleeding or need invasive operation. During the study, any other platelet-elevating drugs will be forbidden.

Drug-associated serious adverse events should be reported to Shanghai General Hospital within 24 h of participating site study staff becoming aware of the occurrence, and a member of Shanghai General Hospital will be on call 24 h a day via telephone. Serious adverse events are defined as any unexpected medical occurrence that meets one of more of the following criteria: 1) Results in death; 2) Is life-threatening; 3) Results in persistent or significant disability/incapacity. If the patient’s injury is directly induced by rhTPO, the cost of the treatment will be covered by the researchers.

### Study population/ participants

A principle investigator (PI), assisted by a well-trained Co-PI in each clinical center, is responsible for selecting eligible patients based on the eligibility criteria and authorizing the staff to have the patients’ consents. Patients are eligible to be enrolled the study based on the following inclusion and exclusion criteria. Inclusion criteria: 1) age ≥ 18 years, and ≤ 75 years, no limitation of gender; 2) Diagnosis or clinical diagnosis of infection; 3) The change of Sequential Organ Failure Assessment (ΔSOFA) ≥ 2; 4) Platelets counts (PCs) < 50 × 10^9^/L; 5) Informed consent. Exclusion criteria: 1) History of the treatments with chemotherapeutic drugs or heparin drugs within six months; 2) History of bone marrow stem cell disorders, malignancy, or immunologic diseases; 3) History of bone marrow, lung, liver, kidney, pancreas, or small bowel transplantation; 4) Confirmed End-stage renal failure (GFR<10 ml/min, Scr>707 μmol/L); 5) Confirmed Disseminated Intravascular Coagulation (DIC); 6) Confirmed Hemorrhagic brain injury or need craniocerebral operation; 7) Died anticipated within 24 h; 8) Pregnant or lactating patients.

### Sample size

The 28-day all-cause mortality of sepsis patients varies in different patient populations. According to the previous studies, the 28-day mortality of sepsis patients with severe thrombocytopenia was more than 50% [19, 20, 31]. Furthermore, in our single-center, retrospective, cohort study, the 28-day mortality of these patients treated with rhTPO was 29.2%. Our sample size was calculated to detect a 20% difference (rhTPO group 30% Vs Control group 50%) in 28-day mortality. Based on a two-tailed test of two independent means, with a significance (α) level of 0.05 and 80% power, a minimum of 91 patients in each group for a total sample of 182 patients was required. It was assumed that the loss rate of this study is no more than 10%, and the minimum sample of this study was 100 patients in each group for a total sample of 200 patients.

### Randomization

Eligible patients will be randomly assigned to the control and rhTPO add-on treatment in a dynamic random and competitive design in clinical trial sites. Sequential organ failure assessment (SOFA), Acute Physiology and Chronic Health Evaluation II (APACHE II) scores are as the dynamic equilibrium factors. Randomization will be done after the first assessment, ensuring that the assessing occupational therapist will not be biased at this time by knowing the group assignment. A random number will be generated before the start of this study. The random number list will be kept by the third party and uploaded into a random data assigned system. When a patient is recruited in this study, the patient will then be assigned a random number by the system with corresponding treatment. If a patient is later excluded for any reason, the patient’s position in the randomization list will not be replaced by any new patient. Patients will be recruited consecutively. After forty patients have been recruited, the dynamic arithmetic will be introduced. Then, the random number assigned by the system will based on the equilibrium of dynamic factors.

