### Outcome measures

#### Primary outcomes

Primary outcome of this study is the 28-day all-cause mortality.

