### Statistical methods

Analyses will be conducted on an intention-to-treat and per-protocol population basis. Data for each assessment will be summarized for each treatment group and the descriptive statistics will be calculated depending on the data distribution for each assessment. Outcomes will be collected at the times defined in the study protocol. The primary efficacy variable will be the change in 28-day mortality. The change in 28-day mortality between the two groups will be analyzed by using Chi-Square. The proportions will be analyzed using logistic regression including baseline as covariate and group as a fixed factor. The comparisons among continuous parametric data were conducted by using t-test or Anova analysis, whereas the A Mann-Whitney U test or a Kruskal-Wallis test were used to analyze continuous nonparametric data. Comparisons between enumeration data ware conducted by Chi-Square or Fisher exact method. Survival comparison between groups was analyzed by using Log-rank analysis. *P* < 0.05 was considered to indicate statistical significance.

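### The primary chi-square uses neither the severity scores that balance the allocation nor centre: a loss of precision and power, not a bias

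*Protocol article*

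**What the plan says.** Study design and setting describes "5 tertiary academic medical centers which are medical, surgical or general ICUs". Randomization describes a "dynamic random and competitive design in clinical trial sites" and states no quota per site. The balancing factors are SOFA and APACHE II ("Acute Physiology and Chronic Health Evaluation II (APACHE II) scores are as the dynamic equilibrium factors", with SOFA named just before). They do not act from the start: "After forty patients have been recruited, the dynamic arithmetic will be introduced". So 40 of the 200 planned patients (20%) are allocated without them. Centre is not listed as a factor.

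On the analysis side, "Primary outcome of this study is the 28-day all-cause mortality", and "The change in 28-day mortality between the two groups will be analyzed by using Chi-Square". A further sentence reads "The proportions will be analyzed using logistic regression including baseline as covariate and group as a fixed factor". It does not say which outcomes it covers or what the baseline term contains. A log-rank comparison is also listed, with no stratification stated. Neither SOFA, APACHE II nor centre is named in any analysis.

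**The concern.** The trial treats severity as important enough to steer the allocation, then sets it aside in the main test. When arms are made alike on a factor that predicts death, the difference in mortality varies less than an unadjusted test assumes. The test then rejects less often than 5% under the null and has less power than the design could deliver.

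Centre raises a related question. Different ICU types enrol in competition and nothing balances the arms within a centre. If mortality differs between centres, chance differences in centre mix add noise to the estimate, and an analysis that knew the centre could remove it.

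What is at stake is efficiency and the precision of one trial's estimate. There is little slack: power at the planned size is only just above 80%.

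**Working it through.** **1. The plan's own figure.** Inputs from Sample size: 50% versus 30% mortality, two-sided 5%, 80% power. Unpooled formula: (1.960 + 0.842)² × (0.50×0.50 + 0.30×0.70) / 0.20² = 90.3, so 91 per group, as stated. Chi-square power is 79.1% with 91 per group and 82.8% with 100. The standard error of the difference at 100 per group is √((0.25 + 0.21)/100) = 6.8 points.

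**2. Noise from centre mix.** The article gives no centre sizes and no mortality by centre, so both are assumed below. With between-centre variance V of control mortality, the chance shift in the mortality difference has mean 0 and SD √(V × 2/100). Five equal centres:

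| Control mortality across centres | V | SD of shift | 95th percentile of absolute shift (simulated) |
|---|---|---|---|
| 40–60% | 0.005 | 1.0 point | 2.0 points |
| 30–70% | 0.020 | 2.0 points | 3.9 points |
| 20–80% | 0.045 | 3.0 points | 5.9 points |

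The simulated SDs (20,000 trials per scenario) are the same. With centre ignored in allocation, the chi-square level was 5.3–5.7% in every scenario, including no centre effect. Centre mix therefore does not inflate it.

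**3. Power from stratifying by centre alone, allocation unchanged.** 200 patients, common odds ratio (0.3/0.7)/(0.5/0.5) = 0.43; uneven enrolment means shares 40/10/10/10/30.

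| Control mortality | Enrolment | Chi-square | Centre-stratified Cochran-Mantel-Haenszel | Change (points) |
|---|---|---|---|---|
| 50% everywhere | equal | 83.2% | 82.3% | −0.9 |
| 50% everywhere | uneven | 83.3% | 82.1% | −1.2 |
| 40–60% | equal | 82.3% | 81.9% | −0.3 |
| 40–60% | uneven | 80.6% | 80.5% | −0.2 |
| 30–70% | equal | 78.3% | 79.8% | +1.6 |
| 30–70% | uneven | 72.8% | 76.9% | +4.1 |
| 20–80% | equal | 68.6% | 75.1% | +6.6 |
| 20–80% | uneven | 57.8% | 69.4% | +11.6 |

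(Changes are taken before rounding.) A second set with assumed centre sizes 70/50/40/25/15 gave 80.2% versus 80.9% at 35–65%, and 73.2% versus 77.2% at 25–75%. Changing which centre has which mortality moved the 35–65% result between 82.8% versus 82.3% and 78.0% versus 79.1%.

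Only the last column measures what stratifying recovers. Part of the fall down the chi-square column comes from holding the odds ratio fixed, which shrinks the overall risk difference. At 20–80% with equal centres, treated mortality is 9.7, 18.8, 30.0, 44.3 and 63.2%, mean 33.2%, so the difference is 50 − 33.2 = 16.8 points instead of 20.

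**4. Why balancing makes the chi-square conservative.** If the arms are balanced on a factor that explains a share s of the outcome variance, the true variance of the difference is (1 − s) times what the test assumes, and the actual level is P(|Z| > 1.96/√(1 − s)).

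- s = 0.020/0.25 = 0.08: threshold 2.04, level 4.1%.
- s = 0.045/0.25 = 0.18: threshold 2.16, level 3.0%.

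Simulation with near-exact balance within five equal strata gave 4.45% and 3.5% (5.5% with no stratum effect, because the counts are discrete). The strata there were centres, but the arithmetic is the same for a severity score.

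**5. The adjusted model.** With allocation balanced on severity, a logistic model with group, centre, SOFA and APACHE II changed power by about −0.7 to +10 points against the chi-square and kept its level at 4.5–5.9%. The chi-square's level fell to about 3.4–4.2% when severity was strongly prognostic. The strength of severity is an assumption; the article does not give it.

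**The case against.** An unadjusted test of a randomised comparison is legitimate, the article is a condensed protocol, and covariate detail usually belongs in the analysis plan. The logistic regression sentence might already cover severity through its undefined baseline term. The first two statements are right in general. But the article is not silent here: it names the test for 28-day mortality, and an analysis plan that adjusted the primary comparison would have to depart from that sentence. The logistic sentence is not tied to the primary outcome and names neither the scores nor centre.

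A reader might infer something stronger: that leaving centre out biases the mortality comparison or inflates false positives, or that centre must be added to the allocation. The documents do not support this. Randomisation keeps the expected shift at zero, the chi-square standard error already covers chance imbalance, and the simulated level did not rise. An SD of 1.0 point against a standard error of 6.8 is (1.0/6.8)² = 2% of the variance; even 3.0 points is 19%. Shared eligibility criteria, guideline care and transfusion thresholds may also narrow centre differences, and balancing on severity removes part of what remains.

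It also stands that no centre sizes or centre mortality are given, that competitive enrolment permits unequal centres without establishing them, and that stratifying by centre alone gains nothing at modest spread.

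**Conclusion.** The point holds as one of efficiency. The primary test ignores the two scores on which the allocation is balanced, and centre. The consequence is lost precision and power, and a conservative test if SOFA and APACHE II strongly predict death.

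The size depends on quantities the article does not give. For severity and centre together, the assumed scenarios run from about −0.7 to +10 points of power. For centre alone the gain is about zero at modest spread and about 4 points at 25–75%. It reaches 4 points at 30–70% only where, as in the uneven case above, 70% of patients sit in the two extreme centres.

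The stronger argument is therefore to analyse by the factors the trial already balances on, with centre added because it is known for every patient. The sample size calculation is not affected. This is a cheap improvement, not a correction of an invalid analysis.

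**What to change.** In Statistical methods, replace the primary chi-square with a logistic model for 28-day death containing treatment group, SOFA, APACHE II and centre. Use the scores as entered for randomisation, and pool very small centres by a rule fixed in advance. Report the covariate-standardised risk difference with its confidence interval, so that the result stays on the scale of the planned 20-point difference. Keep the plain chi-square as a sensitivity analysis. The allocation scheme stays as it is, so an open-label allocation becomes no more predictable.

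The model is affordable. At the planned rates, 100 × 0.50 + 100 × 0.30 = 80 deaths are expected, against seven terms besides the intercept (group, two scores, four for centre), or about 11 deaths per term.

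The cost is a sentence or two in the plan, no new data, and up to about 1 point of power if neither severity nor centre predicts death. The change should be made before outcome data by arm are seen, so that the choice of adjustment cannot be questioned afterwards in an open-label trial.

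### Baseline platelet count is neither a balancing factor nor a named covariate, although the protocol ties it to mortality and transfusion: a small, avoidable loss of precision, not a bias

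*Protocol article*

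**What the plan says.** Under Randomization, the balancing variables are two general severity scores: "Sequential organ failure assessment (SOFA), Acute Physiology and Chronic Health Evaluation II (APACHE II) scores are as the dynamic equilibrium factors". Balancing does not run from the start: "After forty patients have been recruited, the dynamic arithmetic will be introduced". So at most 160 of the 200 patients (200 − 40) are allocated dynamically.

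Platelet count appears elsewhere in three roles:

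- **Entry.** Study population admits patients with "Platelets counts (PCs) < 50 × 10^9^/L".
- **Prognosis.** The Background, citing a multicentre cohort, states that "the greater the extent of thrombocytopenia was, the higher the mortality was".
- **Management and outcomes.** Study design and setting ties platelet transfusion to absolute counts: "when PCs are below 10 × 10^9^/L in the absence of apparent bleeding", "or below 20 × 10^9^/L if the patient has a significant risk of bleeding", and a third threshold of 50 for active bleeding or an invasive operation. Platelet change, recovery time, transfusion and bleeding are all secondary outcomes.

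Statistical methods states a chi-square test for 28-day mortality, t-tests or rank tests for continuous outcomes, chi-square or Fisher tests for counts, and a log-rank test for survival. One sentence provides for logistic regression of proportions with an unspecified baseline covariate.

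**The concern.** By the protocol's own rationale, the starting platelet count bears on the primary outcome and on a whole group of secondary outcomes. Two transfusion thresholds (10 and 20) lie inside the entry range and the third (50) is its upper edge. If one arm happens to receive more patients with very low counts, mortality, bleeding and transfusion can all move the same way in that trial, and the unadjusted tests do nothing to separate this from a drug effect.

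At stake are precision and the credibility of the comparisons closest to the drug's mechanism. The information needed to improve both is in hand at entry, because the count is an eligibility criterion.

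**Working it through.** **1. The plan's own figure.** Inputs from Sample size: 50% versus 30%, two-sided 0.05, power 80%.

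n per arm = (1.960 + 0.842)² × (0.50 × 0.50 + 0.30 × 0.70) / 0.20² = 7.85 × 0.46 / 0.04 = 90.3, so 91. This matches the stated 91. Balancing factors do not enter the formula, so the point does not affect it.

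**2. Inputs the document does not give (assumptions).** Share of entrants in a deeper platelet band: 20–50%. Mortality gap between deeper and shallower entrants: 10, 20 or 30 points. SOFA platelet item: 3 points for 20–49 and 4 points below 20.

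**3. Chance imbalance at 100 per arm.** For share s and gap g:

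- SD of imbalance = sqrt(2 × s × (1 − s) / 100)
- SD of the shift in the mortality difference = g × SD of imbalance

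| s | SD of imbalance (points) | P(imbalance ≥ 10 points) | Shift SD, g = 10 | g = 20 | g = 30 |
|---|---|---|---|---|---|
| 20% | 5.7 | 8% | 0.57 | 1.13 | 1.70 |
| 30% | 6.5 | 12% | 0.65 | 1.30 | 1.94 |
| 40% | 6.9 | 15% | 0.69 | 1.39 | 2.08 |
| 50% | 7.1 | 16% | 0.71 | 1.41 | 2.12 |

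For comparison, the standard error of the mortality difference is sqrt(0.25/100 + 0.21/100) = 6.8 points, and the target difference is 20 points. At s = 30%, one trial in 20 has an imbalance of at least 1.96 × 6.48 = 12.7 points. With a 20-point gap, that moves the mortality difference by 0.20 × 12.7 = 2.5 points.

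**4. Power recovered by balance plus adjustment (91 per arm).** Unadjusted: 0.20 / sqrt(0.46/91) = 2.813; 2.813 − 1.96 = 0.853; power 80.3%. With depth removed, the variance sum falls from 0.46 to 0.46 − 2 × g² × s(1 − s):

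- g = 10: 80.7% at s = 30% and at s = 50%
- g = 20: 81.8% and 82.0%
- g = 30: 83.6% and 84.2%

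**5. Does SOFA balancing already cover it?** Simulation of 3,000 trials of 200 patients per setting: 40 simple randomisations, then a biased coin (0.8) on three bands each of total SOFA and APACHE II, with 30% of patients below 20.

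| Allocation | SD of imbalance in share below 20 (points) | Type I error, unadjusted test |
|---|---|---|
| Simple | 6.3–6.5 | 4.7–5.0% |
| Dynamic on SOFA and APACHE II | 6.3–6.4 | 5.5–5.6% |

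The Monte Carlo standard error of the type I error is sqrt(0.05 × 0.95 / 3000) = 0.4 points, so all these rates are compatible with 5%. Platelet imbalance is essentially unchanged by the dynamic step. The simulation takes the rest of SOFA as independent of platelet count; a positive correlation would make SOFA a somewhat better proxy.

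**6. Recovery definition.** Every entrant starts below 50, so a rise of 50 always ends below 100. The rise limb asks the same of everyone; only the limb at 100 depends on the starting count.

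**The case against.** The strongest reply is that this is a preference, not a defect. Two severity scores are a defensible choice for a mortality trial, nothing in the article says SOFA is meant to stand in for platelet depth, and any prognostic variable could be proposed as a further factor. The mortality effect is small on every assumed input. The logistic sentence already foresees a baseline covariate, and naming covariates is commonly left to an analysis plan, which is not shown here.

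Most of this stands. Omitting the factor is neither an error nor a contradiction. Two parts do not fully answer the point. The article itself fixes the balancing factors, and allocation cannot be repaired by a later analysis plan. It also states unadjusted tests for mortality and for the continuous platelet outcomes, so adjustment is not the plan as written.

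Three stronger readings are tempting but unsupported:

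- **That the omission biases the trial.** Chance imbalance is part of the sampling error the tests allow for, and type I error stays near 5%.
- **That SOFA carries no platelet information.** Its cut-points are not in the document, and even a split of 3 versus 4 points carries some.
- **That transfusion and recovery follow directly from the starting count.** The threshold of 20 applies only to patients at significant bleeding risk, and the rise limb of recovery is the same for all.

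**Conclusion.** The point holds as a minor design and analysis improvement. A variable that the protocol itself treats as prognostic is neither balanced nor named for adjustment. The cost for mortality is a shift with an SD of about 0.6–2.1 points and up to about 4 points of power (80.3% to 80.7–84%). There is no systematic bias and no effect on the stated 91 per arm.

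These figures rest on the assumed share of deep thrombocytopenia, the assumed mortality gap and, for the proxy argument, the assumed SOFA bands. The Background gives a direction for mortality by depth but no figures within the range below 50, so the gap could be small. The effect on transfusion and platelet outcomes is probably larger, because the thresholds are absolute counts. The document gives no rates by starting count, so no size can be put on it.

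**What to change.** Prespecify the last platelet count before randomisation, preferably continuous, as a covariate in the 28-day mortality model and in the analyses of platelet change, transfusion, bleeding and recovery time. State explicitly that it is the pre-randomisation value: Data collection has baseline laboratory results tested within 24 hours after randomisation and keeps the lowest or worst value of a day, so its baseline could be a post-randomisation count. Alongside the adjusted model, report a standardised risk difference for mortality, so that the result stays on the scale of the planned 50% versus 30%.

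If the allocation system can still be changed, also add the count (<20 versus 20–49 × 10⁹/L) as a third dynamic factor. If it cannot, covariate adjustment alone recovers most of the benefit.

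The cost is one extra model term. The article does not give recruitment status; the trial was registered in 2016 and this is version 3 from 2019. If recruitment has begun, the third factor would need a documented change to the allocation algorithm, which is more than a configuration setting.
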